## Methods

### Study protocol

This is a single-center, currently ongoing study, conducted at the Rehabilitation Center for Communication Disorders of the Department of Otorhinolaryngology of the Antwerp University Hospital, Belgium. Subjects are invited to participate in the study if they meet the following inclusion criteria: (1) The subject meets the Belgian national criteria for reimbursement of a cochlear implant, (2) the subject suffers from a postlingual hearing impairment, (3) the subject is scheduled for a first cochlear implantation and (4) the subject is aged 55 or older. The national criteria for reimbursement of a cochlear implant are (A) bilateral severe to profound hearing loss (pure tone average at 500, 1000, and 2000 Hz equal to or exceeding 85 dB HL), (B) brainstem evoked response audiometry results in a threshold of peak V at 90 dB nHL or more and (C) speech recognition scores of 30% or less for Dutch open-set monosyllabic words presented at 70 dB SPL in quiet in the best aided condition. Subjects who do not meet the national criteria for reimbursement and pay the implantation themselves are not included in the study. The case is multidisciplinary evaluated, all contra-indications for cochlear implantation are to be taken into account and the expectations of the person toward the rehabilitation process and the outcomes are thoroughly discussed by the clinician to remain realistic.

The participants are evaluated by an experienced, Good Clinical Practice (GCP) certificated audiologist (Master of Science) prior to implantation and subsequently 6 months and 12 months after activation of the speech processor and annually from then on (Table 1). The test battery consists of a cognitive assessment to evaluate five different cognitive domains, an audiological examination, four questionnaires to assess the impact of the hearing disability and the quality of life (QoL), and a semi-structured interview in which the self-reliance of the patient is discussed.

**Table 1 T1:** **Time schedule of assessments and intervention**.

	**Preoperatively**	**Cochlear implantation**	**6 months** after first fitting	**12 months** after first fitting	**yearly**
					
Cognition	RBANS-H		RBANS-H	RBANS-H	RBANS-H
MOM	Tone audiometry		Tone audiometry	Tone audiometry	Tone audiometry
	- unaided (inserts)		- unaided (inserts)	- unaided (inserts)	- unaided (inserts)
	- aided (free field)		- aided (free field)	- aided (free field)	- aided (free field)

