### Primary outcome measurement: RBANS-H

The primary outcome measurement is the change in cognitive capabilities following implantation, as measured by means of the Repeatable Battery for the Assessment of Neuropsychological Status (RBANS, Randolph et al., 1998), adjusted to test Hearing impaired subjects (RBANS-H). The RBANS assesses five cognitive domains, i.e., *Immediate Memory, Visuospatial/constructional, Language, Attention*, and *Delayed Memory* (Table 2). The test consists of 12 subtests and the score on each subtest contributes to one of the five domains. The Dutch version of the original English RBANS is obtained by the process of forward-backward translation. In order to test subjects with a severe hearing impairment a number of adjustments to the standard RBANS had to be made (Phillips, 2016). The administration of the test is accompanied by the use of a PowerPoint presentation shown on an external computer screen connected to a laptop. By means of this presentation all the oral instructions are supported by written explanations to ascertain that the subject understands the instruction even though he or she does not hear what is being said. In addition, the stimuli in the subtests *List Learning, Story Memory, Digit Span*, and *List Recognition* are not only presented auditorily but also visually, making it possible to test the subject in the same reliable way before and after implantation. All the adjustments were made in accordance to the guidelines of the RBANS, as discussed in the manual on page 15 “Testing Examinees With Physical or Language Impairments” (Randolph, 2012). The RBANS was ordered on the website of Pearson Clinical (http://www.pearsonclinical.com).

**Table 2 T2:** **The five cognitive domains and twelve subtests of the RBANS**.

**Immediate memory**	**Visuospatial/ constructional**	**Language**	**Attention**	**Delayed memory**
(1) List Learning	(3) Figure Copy	(5) Picture Naming	(7) Digit Span	(9) List Recall
(2) Story Memory	(4) Line Orientation	(6) Semantic Fluency	(8) Coding	(10) List Recognition
				(11) Story Recall
				(12) Figure Recall

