The domain *Immediate Memory* consists of two subtests: *List Learning* and *Story Memory*. In the first subtest, 10 semantically unrelated words are orally and visually presented to the subject. The words are presented on an external screen in lowercase e letters at a 2-s rate. Within the 2-s period the item is visible to the subject for 1.25 s, followed by a 0.75-s interval between the items. The examiner reads the words aloud when they appear on the screen so the subject receives audio-visual information. The subject is asked to repeat as many words as possible after each of four learning trials. In the second subtest, *Story Memory*, a twelve-item short story is presented over two trials. The story is presented visually in three separate parts and read aloud simultaneously at a slow reading speed. After each presentation the subject is asked to recall as much of the story as he or she can remember. A verbatim criterion is used.

The next two subtests, *Figure Copy* and *Line Orientation*, contribute to the second cognitive domain *Visuospatial/constructional*. The first subtest involves copying a geometric figure comprising ten parts, each evaluated for correctness and completeness on the one hand and proper location in relation to the rest of the figure on the other hand. The figure remains visually available while copying. In the second subtest of the *Visuospatial/Constructional* domain, a series of 13 identical lines, radiating out from a single point and spanning 180 degrees, are shown. Below this semi-circular, fan-shaped pattern of numbered lines (1–13), two lines of equal length that match two of the lines from the array are displayed. The subject is asked to give the numbers or point to the two lines that are identical in orientation to the two target lines.

The cognitive domain *Language* includes the subtests *Picture Naming* and *Semantic Fluency*. In the first subtest, 10 line drawings are to be named by the subject. In case of an obvious misperception, a semantic cue is given. The second subtest involves the generation of as many examples as possible from a given semantic category such as fruits and vegetables within 1 min.

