### Statistics and anticipated results

The sample size calculation is based on the primary outcome variable, RBANS-H total score. A sample of 19 persons is needed to obtain 80% power using a paired *t*-test to detect a Cohen's d of 0.7 at an alpha level of 0.05. Due to the age of the study population and the duration of the longitudinal study, a 20% dropout rate is taken into account. The targeted total sample size is therefore adjusted to 25.

Descriptive statistics will be used to summarize the mean/median, standard deviation, and possible ceiling or floor effects of the different variables. The effect of the treatment on the primary outcome will be modeled using linear mixed models. *Post-hoc* comparisons will be carried out to test for differences in outcomes between the different time points, using Tukey's correction for multiple comparisons. In order to avoid statistical threats such as regression toward the mean, data will be analyzed as a whole, and not split up into groups based on the cognitive performances. The most recent version of IBM SPSS Statistics (IBM; Armonk, NY) and R (R Development Core Team; Vienna, Austria) will be used for the analyses.

Given the previous study conducted by Mosnier et al. (2015) it is hypothesized that, in general, the cognitive abilities of the older adults will increase at 6 and12 months after implantation. After this initial increase a gradual decrease in cognition is expected, similar to the age-related cognitive decline in normal hearing subjects. In other words, the authors expect the RBANS-H total percentile to increase during the first year after implantation, i.e., the hearing impaired participants will catch-up with the normal hearing norm group of the RBANS, and stabilize over the next nine years, i.e., the hearing impaired participants will show a cognitive decrease similar to the norm group.

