**Table 4 T4:** **A schematic representation of the comparison between MoCA and RBANS**.

	**MoCA**	**RBANS**
Languages	>50 languages	English and Spanish
Public domain?	Yes	No
Duration	10–15 min	±30 min
Differentation in level of cognition	Normal *OR* mild cognitive impairment (screening)	Normal *TO* moderately severe dementia (scaled scores and percentiles with extensive normative data)
Index scores per cognitive domain	No	Yes (5)
Sensitivity to change	Limited	Good (+90 and 95% confidence intervals for the overall score and each index score)

Adding visual support to the subtests *List Learning, Story Memory, Digit Span*, and *List Recognition* was considered necessary to test the hearing impaired subjects in a reliable and identical manner before and after implantation and to ascertain that a possible improvement on the cognitive test cannot be attributed to the improved hearing with the CI (Phillips, 2016). According to the study of Delogu et al. (2009), the addition of visual stimulation in a verbal auditory memory task has no significant effect on the number of words repeated by the subjects. Since the auditory presentation is dominant in the case of verbal stimuli and there is no additional benefit from a bimodal (written and spoken) encoding of words, the modifications performed in this study are hypothesized to have little impact on the results. Nevertheless, these modifications may still have a small effect on the test scores and may invalidate the rigid use of the norms. By exploring the change in test and index scores, rather than the test and index scores *per se*, the effects of the modifications are reduced to the minimal.

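### Visual support does not rule out better hearing as a source of RBANS-H gain, because four subtests are also read aloud at every visit

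*Protocol article*

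**What the plan says.** The primary outcome is change in RBANS-H after implantation. On the score used, Statistics and anticipated results states: "The sample size calculation is based on the primary outcome variable, RBANS-H total score".

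Under Primary outcome measurement: RBANS-H, the stimuli of List Learning, Story Memory, Digit Span and List Recognition "are not only presented auditorily but also visually". For List Learning: "The examiner reads the words aloud when they appear on the screen so the subject receives audio-visual information". For Story Memory: "The story is presented visually in three separate parts and read aloud simultaneously at a slow reading speed". Digit Span and List Recognition are described in the same two-channel way.

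Entry (Study protocol) requires, among other criteria, "speech recognition scores of 30% or less for Dutch open-set monosyllabic words" in the best aided condition. At postoperative visits the speech processor is fitted if needed, then the audiological battery is run, then the RBANS-H (Stepwise procedures).

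The Discussion gives one purpose of the visual support as being "to ascertain that a possible improvement on the cognitive test cannot be attributed to the improved hearing with the CI". It supports this with a cited study in which adding visual stimulation to an auditory verbal memory task made no significant difference, and with the argument that begins "Since the auditory presentation is dominant in the case of verbal stimuli" and goes on to say that presenting words in both forms brings no extra benefit. It grants a possible small effect on scores, and says that by looking at change "the effects of the modifications are reduced to the minimal".

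**The concern.** The procedure is the same at each visit, but what the participant takes in need not be. Before implantation the spoken channel is largely unusable, so the words, story and digits arrive mainly as text. After implantation the same material can be both read and heard. If hearing the material helps encoding, the score can rise with no change in cognition, in the direction the study hypothesises for 6 and 12 months.

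This affects the meaning of the primary outcome. It also touches the second aim, relating cognition to audiometric performance, because better aided hearing could raise part of the cognitive score directly and so contribute to the association under study.

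**Working it through.** **1. Input received, before and after**

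| | Before implantation | After implantation |
|---|---|---|
| Text on screen | yes | yes |
| Examiner's voice | yes | yes |
| Usable hearing | pure tone average of 85 dB HL or worse on both sides; at most 30% best-aided word recognition at 70 dB SPL in quiet | implant active; processor fitted if needed before testing |
| Likely input | mainly visual | audio-visual |

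The article does not say that the voice or the device is switched off during the RBANS-H. That the implant is worn is inferred from the order of procedures.

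**2. The three supports for the claim**

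- *Cited study.* As described, it compares auditory with auditory plus visual presentation. The contrast here is visual with visual plus auditory.
- *Dominance and no bimodal benefit.* The stated reason is that audition already carries the task. That speaks to adding text for someone who hears. It is not shown to cover adding sound for someone who was reading.
- *Change scores.* Let the true cognitive change be Δ and the modality effect m₀ at baseline and m₁ at follow-up. The expected observed change is Δ + (m₁ − m₀). The second term vanishes only if m₁ = m₀, and the hearing criteria give reason to doubt that.

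**3. Reach (Table 2 and the subtest descriptions)**

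| Domain | Exposed | Not exposed |
|---|---|---|
| Immediate Memory | List Learning, Story Memory (2/2) | none |
| Visuospatial/constructional | none (0/2) | Figure Copy, Line Orientation |
| Language | none (0/2) | Picture Naming, Semantic Fluency |
| Attention | Digit Span (1/2) | Coding |
| Delayed Memory | List Recognition; List Recall and Story Recall through encoding (3/4) | Figure Recall |

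Total: 2 + 0 + 0 + 1 + 3 = 6 of 12 subtests, in 3 of 5 domains. List Recognition is probably affected least, since each word stays on screen at the participant's own pace.

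**4. What a shift could do (illustration)**

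The plan's own figure first. For a two-sided paired t-test with d = 0.7 and alpha 0.05, the noncentrality is d√n = 0.7 × √19 = 3.05, with 18 df and critical value 2.10. Power is 0.823, so the stated n = 19 is reproduced.

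Now set Δ = 0 and assume that hearing alone shifts the change by b SD of the change. The documents give no value for b. The chance of declaring improvement with n = 19 is:

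| b (assumed) | b√19 | Unadjusted paired t (critical 2.10, 18 df) | Tukey over three visits (critical 2.44, 36 df) |
|---|---|---|---|
| 0.2 | 0.87 | 13% | 7% |
| 0.3 | 1.31 | 24% | 14% |
| 0.4 | 1.74 | 38% | 26% |

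With b = 0 the unadjusted rate is 2.5%. The Tukey column is per comparison and nearer the planned analysis (linear mixed model, Tukey-corrected comparisons), but it simplifies that model. More annual visits would raise the critical value and lower these rates.

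**The case against.** The strongest reply has five parts.

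- **The protocol argues against a bimodal gain.** It says that written plus spoken encoding adds nothing. This stands as a reason not to assume a gain. A reader might infer from the dominance of audition that implantation must raise scores. The documents do not support that, because audition can be dominant without adding to legible text. But neither does the clause, as argued, show that adding sound to text has no effect.
- **The data can already help.** A reader might infer that nothing planned could separate the two explanations. That goes too far. Change in index scores is to be explored, two domains contain no spoken stimuli, and relating cognition to audiometry is a stated aim. What the article lacks is a stated comparison and a rule for reading it.
- **The wording is hedged.** The claim is a statement of purpose, and a possible small effect on scores is admitted. However, the consequence drawn from that admission concerns the use of norms, and the remedy offered is the change score, which does not remove this effect.
- **The study disclaims causality.** It is exploratory and has no control group. This limits the harm, but the disclaimer concerns cognition changing over time. The issue here is a score that could change without cognition changing.
- **Visual support helps.** It does reduce the hearing confound relative to speech-only testing. That stands, and the corrected wording should say so.

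**Conclusion.** The assurance that improvement cannot be put down to better hearing is not supported as written. The input received is likely to differ between baseline and follow-up, the cited evidence as described addresses the opposite contrast, and any difference stays in the change score. Up to 6 of 12 subtests in 3 of 5 domains are open to it, all contributing to the primary total, and a gain from regained hearing would favour the hypothesis.

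This rests on two inferences: that the implant is worn during cognitive testing, and that baseline input is mainly visual. Residual hearing or lip-reading before surgery would narrow the gap.

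The size is unknown. The percentages above depend on assumed shifts and are not estimates of bias in this study. A reader might also conclude that a gain confined to the spoken-stimulus subtests is hearing and not cognition. That does not follow: these subtests make up all of Immediate Memory and three of the four in Delayed Memory, so a true verbal memory gain would appear in the same place. The supportable statement is that the two cannot be told apart.

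**What to change.** 1. In the Discussion, replace the claim with a statement that visual support reduces, but does not exclude, a contribution of improved hearing to change in RBANS-H. Remove the assurance that using change scores minimises this effect.
2. Pre-specify, beside the total and in the same mixed model, change in a composite of the six subtests without spoken stimuli: Figure Copy, Line Orientation, Picture Naming, Semantic Fluency, Coding and Figure Recall.
3. State in advance that a gain confined to the spoken-stimulus subtests cannot be distinguished from improved hearing.
4. Keep the test presentation as it is. A change part-way would split about 25 participants across two versions.

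Cost: wording and one further analysis on subtests already collected. The composite is less reliable than the total and covers little memory (Figure Recall only), so absence of a gain on it would not show that a gain on the total was due to hearing. It is also not wholly free of speech, since instructions are given orally with written support and Picture Naming allows a semantic cue.

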## Conclusion

The proposed exploratory study aims to give more insight into the cognitive profile of severely to profoundly hearing impaired older adults before and after cochlear implantation and into the relationship between their cognitive capabilities, audiometric performances, quality of life and self-reliance. The study may be a next step for future research investigating the relationship between hearing loss and cognition and the effects of cochlear implantation on this relationship, as to whether cognitive tests are important during the CI selection process and the rehabilitation and whether cochlear implantation could extend the period of independence in the older population.

## Dissemination

According to the Standard Protocol Items: Recommendations for Interventional Trials (SPIRIT) guidelines, the authors declare that a clinical article will be written on the primary and secondary outcomes of the study and will be disseminated regardless of the magnitude or direction of effect. The present trial is not industry initiated; therefore, there are no publication restrictions imposed by sponsors. In addition, a full study report, anonymized participant-level dataset and statistical code for generating the results will be made publicly available no later than 3 years after termination of the study for sharing purposes.

## Abbreviations

CI: Cochlear Implant
dB HL: Decibel Hearing Level
dB SPL: Decibel Sound Pressure Level
dBnHL: Decibel normal Hearing Level
GCP: Good Clinical Practice
HADS: Hospital Anxiety and Depression Scale
HISQUI19: Hearing Implant Sound Quality Index-19
Hz: Hertz
LIST: Leuven Intelligibility Sentences Test
MMSE: Minimental State Examination
MoCA: Montreal Cognitive Assessment
MOM: Minimal Outcome Measurements
NCIQ: Nijmegen Cochlear Implant Questionnaire
NVA: Nederlandse Vereniging voor Audiologie
QoL: Quality of Life
RBANS: Repeatable Battery for the Assessment of Neuropsychological Status
RBANS-H: Repeatable Battery for the Assessment of Neuropsychological Status for Hearing impaired patients
SPIRIT: Standard Protocol Items: Recommendations for Interventional Trials
SRT: Speech Reception Threshold
SSQ12, Speech: Spatial and Qualities of Hearing scale-12
WAIS: Wechsler Adult Intelligence Scale.
